### Allocation

Participants will be assigned to the experimental GLB-CVA or waitlist control groups using computer-generated random numbers in Microsoft Excel. Individuals in the waitlist control will be placed on a waiting list and receive the intervention after a 6-month period. To ensure an equal distribution between groups, block randomization will be used with blocks of sizes 4 and 6. Randomly mixing block sizes will reduce the study coordinator’s ability to predict the last assignment of each block. The randomization list will be generated by the biostatistician, with results contained in sealed envelopes labeled with study identification numbers. After a participant is enrolled in the study, a study coordinator will select the assigned envelope to reveal the participant’s group. Owing to the type of intervention, it is not practical to blind study participants to group assignment. However, to minimize assessor bias, outcome assessments will be conducted by a coordinator who (1) is blinded to group assignment, (2) is not included in study team meetings, (3) has a script to remind participants at the beginning of each assessment to maintain blinding, and (4) has a process for recording unblinding.

### Data Management, Quality Assurance, and Exclusion of Bias

All nonelectronic source documents will be kept in a locked storage cabinet in the Baylor Scott and White Institute for Rehabilitation research office. Case report forms and all outcomes data will be inputted into REDCap (Vanderbilt, TN), a Health Insurance Portability and Accountability Act–compliant (21 Code of Federal Regulation Part 11) secure Web-based program, by trained study staff. All electronic data will be stored and maintained on a secure server and disposed in accordance with current federal guidelines.

Data management activities will occur quarterly and include data quality checks and verification, as well as internal logic checks (eg, outlier values and internal inconsistencies). Of the participant files, 10% will be audited for source document and data entry review. Cross-tabulation checks using SAS will also be applied to the data. Data will be stored and backed up periodically by the biostatistician on the secure server. Descriptive statistics will be prepared and included into quarterly reports to ensure the quality of data and study progress. The principal investigator will provide oversight on all data entry and proper data monitoring and audit procedures.

### Statistical Methods

To examine adherence to the GLB-CVA intervention (Aim 1), univariate analysis will be used to summarize session attendance to determine if it reaches the hypothesized rate of at least 70% (15/22). An RCT will be completed to examine the efficacy of the GLB-CVA on primary and secondary outcomes in the intervention group compared with the waitlist control group at 3, 6, and 12 months from baseline. General mixed modeling analysis will be conducted for the primary and secondary outcomes to assess initial and sustained impacts of the adapted GLB-CVA intervention. More specifically, individual growth models will be evaluated for linear and nonlinear change from baseline to 3, 6, and 12 months (level 1, time effects), overall group difference (level 2, group effect), and group difference in change (cross-level, time-by-group interaction effect; Hypothesis 2.1). Models will be adjusted for demographic variables (eg, age, gender, ethnicity, and disability severity using the Modified Rankin Scale), particularly if they are imbalanced after randomization, thereby providing more accurate estimates of the intervention impacts.

Separate growth models for change from baseline to 12 months will be fitted within both groups combined (time effects only; Hypothesis 2.2). Data will include missing observations resulting from either attrition or nonresponse. Intent-to-treat analysis will use restricted maximum likelihood estimation, which can produce unbiased estimates with incomplete data. In addition, sensitivity analysis will utilize iterative Monte Carlo Markov Chain multiple imputation for missing data. All selected variables will be used in the imputation process, allowing for greater recovery of the missing data. All analyses will be performed using SAS 9.4.

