### Objectives

#### Aim 1

Aim 1 of this study is to examine adherence to GLB-CVA intervention participation.

*Hypothesis:* Intervention participants will attend at least 70% (15/22) of the weekly and monthly group-based sessions [18].

#### Aim 2

Aim 2 of this study is to conduct an RCT to examine the efficacy of the GLB-CVA on primary and secondary outcomes in the intervention group, compared with the waitlist control group at 3 and 6 months from baseline.

*Hypothesis 2.1:* The intervention group will demonstrate statistically significant improvements in our primary (weight) and secondary outcomes (activity assessed with accelerometers, waist and arm circumference, blood pressure, hemoglobin A_1c_, fasting glucose and lipid panel, 8-year diabetes risk, functional measures, self-report measures of physical activity and healthy eating, executive function, perceived social support, self-rated abilities for health behavior practices, pain interference, sleep disturbance, habits, and quality of life) when compared with the waitlist control group at 3 and 6 months.*Hypothesis 2.2:* Combined intervention data from both groups will demonstrate significant improvements in primary and secondary outcomes after 3, 6, and 12 months.

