### Outcome Measures

Participants will complete assessments at 4 time points over the course of the yearlong intervention, including baseline, 3, 6, and 12 months. The waitlist control group will complete 2 additional assessment periods that serve as data for comparison in the RCT before they undergo the 12-month intervention. Demographic data collected will include the following: type of stroke, severity of disability (Modified Rankin Scale [29]), current age, date of stroke, sex, parental history of diabetes, race and ethnicity, education level, premorbid history of mental illness, marital and relationship status, diagnosed medical conditions, previous and present smoking and cigarettes per day, alcohol consumption and drinks per week, residence status and zip code, annual household income category, pre- and current stroke insurance type, pre- and current employment status, prestroke and current weight, height, and resting metabolic rate with MedGem. The primary and secondary outcomes are outlined in Multimedia Appendix 2 [30-49]. Participants will be compensated US $25 for their participation at each study time point. Assessments will be completed by a data collector who is trained as a medical assistant and phlebotomist and has completed Modified Rankin Scale training for previous stroke studies.

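### The randomised comparison is planned out to 12 months although the waitlist arm starts the programme at 6 months, so the efficacy test is contaminated and can change sign

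*Protocol article*

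**What the plan says.** Four sections of the protocol article bear on the point.

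- **Objectives, Aim 2.** The intervention group is to be "compared with the waitlist control group at 3 and 6 months from baseline". Hypothesis 2.1 uses the same two time points. Twelve months appears only in Hypothesis 2.2, which combines the intervention data of both groups.
- **Allocation.** "Individuals in the waitlist control will be placed on a waiting list and receive the intervention after a 6-month period".
- **Outcome Measures.** The waitlist group has "2 additional assessment periods that serve as data for comparison in the RCT before they undergo the 12-month intervention".
- **Statistical Methods.** Efficacy is to be examined "in the intervention group compared with the waitlist control group at 3, 6, and 12 months from baseline". The method is that "individual growth models will be evaluated for linear and nonlinear change from baseline to 3, 6, and 12 months", and the between-group part of that model is labelled "time-by-group interaction effect; Hypothesis 2.1". A separate sentence then covers the combined-group model for Hypothesis 2.2.

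**The concern.** The first three sections describe a comparison that ends at month 6. The Statistical Methods describe one that ends at month 12. Because Hypothesis 2.2 has its own sentence there, the 12-month time point cannot be read as a stray reference to the combined analysis.

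At 12 months from baseline the waitlist arm has had about 6 months of GLB-CVA. A month-12 contrast therefore compares people late in the programme, when earlier studies show some of the effect fading, with people at the 6-month point of it. A growth slope through month 12 mixes that contrast with the valid months 0 to 6. The slope-by-group term is the efficacy test for weight, the primary outcome. A programme that works as the protocol assumes could be reported as ineffective, or as worse than waiting. Any statement about lasting effect beyond month 6 would have no randomised support.

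**Working it through.** **Inputs.** From Sample Size: 32 per group; d = 0.99, 0.91 and 0.74 at 3, 6 and 12 months; a 4% group difference with 95% power; attrition of 23% at 6 months and 33% at 12. From Allocation: the waitlist arm starts after 6 months.

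**Assumptions.** Two-sided alpha of 0.05 (not stated). The d values, which describe weight loss over time in earlier general-population studies, are used as between-group effects. The untreated waitlist arm stays flat.

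**1. The protocol's power figure.** With d = 0.91 and n = 32 per arm, d·√(n/2) = 0.91 × 4 = 3.64, and Φ(3.64 − 1.96) = 95.4% (94.8% with the t distribution). This matches the stated 95%. No SD is given for the 4% difference; d = 0.91 implies 4/0.91 ≈ 4.4 percentage points. With 21 per arm (33% attrition), the t-based power is 82.1% for d = 0.91 and 87.9% for d = 0.99, close to the stated 83% to 87%. The power statement is not in dispute.

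**2. Expected profiles** (SD units, negative = weight loss), with a full waitlist response after month 6:

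| Month | 0 | 3 | 6 | 12 |
|---|---|---|---|---|
| GLB-CVA | 0 | −0.99 | −0.91 | −0.74 |
| Waitlist | 0 | 0 | 0 | −0.91 |
| Difference | 0 | −0.99 | −0.91 | +0.17 |

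**3. Linear slopes through month 12.** For t = 0, 3, 6, 12 the mean is 5.25 and Σ(t − 5.25)² = 78.75.
- GLB-CVA: [(−2.25)(−0.99) + (0.75)(−0.91) + (6.75)(−0.74)]/78.75 = −3.45/78.75 = −0.0438 per month.
- Waitlist: (6.75)(−0.91)/78.75 = −6.1425/78.75 = −0.0780 per month.
- Difference: +0.0342 per month, the wrong sign. Over 6 months it implies +0.21 instead of −0.91.
- Months 0 to 6 only: −(3 × 0.91)/18 = −0.152 per month, or −0.91 over 6 months.

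**4. Dependence on how well the waitlist arm responds** (share of the 0.91 effect reached by month 12):

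| Share | Month-12 difference | Linear slope difference × 12 |
|---|---|---|
| 0% | −0.74 | −0.53 |
| 50% | −0.29 | −0.06 |
| 75% | −0.06 | +0.18 |
| 100% | +0.17 | +0.41 |

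The sign changes at 0.74/0.91 = 81% for the contrast and 3.45/6.1425 = 56% for the slope.

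**5. Effect on the test.** Take per-subject slopes, independent visit errors with variance 0.5 (so a change between two visits has SD 1) and 32 per arm.
- The standard error of the 0-to-12 slope difference is √(0.5/78.75) × √(2/32) = 0.0199.
- Full response: 0.0342/0.0199 = 1.72. The test favours the waitlist significantly in Φ(1.72 − 1.96) ≈ 40% of trials and GLB-CVA in well under 1%.
- Half response: the difference is −(3.45 − 3.07)/78.75 = −0.0048, and 0.0048/0.0199 = 0.24. GLB-CVA is favoured in Φ(0.24 − 1.96) ≈ 4% of trials.
- Months 0 to 6 only: the standard error is √(0.5/18) × √(2/32) = 0.0417, and 0.152/0.0417 = 3.64, so power is about 95%.

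The 40% depends on the covariance. Simulations with random slopes as well as residual error gave about 15% to 18%. GLB-CVA was favoured in under 0.5% of trials under every structure tried with a full waitlist response.

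**The case against.** Four points can be made for the plan.

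- **The plan allows nonlinear change.** A quadratic fit to the same profiles gives a 0-to-6-month difference of −0.97 SD, close to the true −0.91. In simulation its 6-month contrast favours GLB-CVA in about 97% of trials. This stands: the 6-month effect is lost under a linear fit, not under every fit. But the quadratic still gives about +0.19 at month 12, and the conclusion then depends on which curve is chosen.
- **Outcome Measures describes the waitlist comparison data as collected before that arm's programme.** If later waitlist data stay out of the model, the waitlist slope is about zero and the sign does not reverse. That is a sensible intention, but it leaves no waitlist observation for the 12-month comparison that the Statistical Methods announce.
- **Reversal is conditional.** It needs a waitlist response above 56% (slope) or 81% (contrast). If both arms are forced through a common baseline, the linear slope keeps its sign even at full response. This stands as a limit on the size. The loss is still large: the common-baseline slope falls in size from 17.31/189 = 0.092 to 6.39/189 = 0.034 per month, or 63%.
- **The repair is editorial, because the aims are already right.** True, but the Statistical Methods are the text an analyst follows.

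Reading 12 months as time since each arm's own start does not help either: it compares treated with treated.

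**Conclusion.** The concern holds. The Statistical Methods contradict the Objectives, Allocation and Outcome Measures, and the analysis as written has no untreated control at its last time point. With the protocol's own effect sizes and a full waitlist response, the month-12 difference moves from −0.74 SD (had the control stayed untreated) to +0.17 SD, and the linear time-by-group slope from −0.044 to +0.034 SD per month. With a half response the signs hold, but power for the linear test falls to about 4%.

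These sizes rest on a flat untreated control, on earlier-study d values used as between-group effects, and on an assumed covariance. Reversal is possible rather than certain. Contamination of the month-12 contrast does not depend on the curve fitted; only a zero response in the waitlist arm would remove it.

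**What to change.** In the Statistical Methods, limit the comparison with the waitlist group to months 3 and 6. Fit the Hypothesis 2.1 model to the baseline, 3-month and 6-month assessments only, and remove month 12 from the time-by-group term. State that 12-month results are uncontrolled, within-group findings that belong to Hypothesis 2.2, and that effects beyond month 6 are not assessed against a randomised control.

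The cost is wording. Data collection and sample size do not change. Power at 6 months stays at about 95% with 32 per arm, and at 88% to 89% after 23% attrition (0.77 × 32 = 24.6 per arm, d = 0.91). The only loss is a 12-month between-group claim that the design cannot support.

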### Sample Size

For the proposed study, 64 participants (32 per group) will be enrolled. The sample size was calculated to ensure that we have sufficient power for our analyses on the primary outcome (weight). Previous GLB studies with the general population have demonstrated weight loss over time (median *d*=0.99 at 3 months, 0.91 at 6 months, and 0.74 at 12 months) [15-18]. Results also indicated a maximum attrition rate of 16%, 23%, and 33% at 3, 6, and 12 months, respectively. Thus, a sample size of 64 will allow a power of greater than 90% to detect a conservatively assumed group difference of 4% in weight change (95% power). In the event of 33% attrition, we will achieve 83% to 87% power to detect these differences.

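### The primary weight comparison is not reduced to one contrast: no deciding visit is named, and the growth model's time form is left open and runs past the randomised period

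*Protocol article*

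**What the plan says.** All references are to the protocol article.

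- **Objectives, Hypothesis 2.1.** "The intervention group will demonstrate statistically significant improvements in our primary (weight) and secondary outcomes", and this is to hold "when compared with the waitlist control group at 3 and 6 months". Neither visit is named as decisive.
- **Statistical Methods, time points.** The same randomised comparison is described as "compared with the waitlist control group at 3, 6, and 12 months from baseline".
- **Statistical Methods, model.** The text says that "individual growth models will be evaluated for linear and nonlinear change from baseline to 3, 6, and 12 months (level 1, time effects"). It then lists "overall group difference (level 2, group effect") and "group difference in change (cross-level, time-by-group interaction effect; Hypothesis 2.1"). The hypothesis label is attached to the interaction only.
- **Allocation.** Waitlist participants receive the intervention after 6 months.
- **Sample Size.** There are 32 per arm. Earlier studies gave a median standardised weight loss of 0.99 at 3 months, then "0.91 at 6 months, and 0.74 at 12 months". Power of 95% is claimed for a 4% group difference in weight change, with no visit attached, and 83% to 87% after 33% attrition.

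**The concern.** A primary comparison should come down to one estimate and one test. Here two things remain open.

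The first is the visit. The hypothesis names two, and the analysis section adds a third. At that third visit, 12 months after randomisation, the waitlist arm is about 6 months into its own intervention (12 − 6), so a growth curve fitted through it no longer compares treated with untreated participants.

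The second is the time form. A linear model has one time-by-group term and a quadratic model has two, and these terms measure different things. Until the form is fixed, the interaction is not one test.

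At stake are control of the false-positive rate on the primary outcome, the meaning of the reported weight effect, and the link to the power calculation, which assumes a single contrast.

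**Working it through.** **Inputs.** From Sample Size: 32 per arm, d = 0.99, 0.91 and 0.74 at 3, 6 and 12 months, a 4% difference and 33% attrition. Assumed, because not stated: two-sided 5% per test, and d = 0.91 as the standardised equivalent of 4% (implied SD 4 / 0.91 ≈ 4.4 percentage points).

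**1. The plan's own power.** For one two-group contrast, power ≈ Φ(d√(n/2) − 1.96).
- n = 32, d = 0.91: 0.91 × 4 − 1.96 = 1.68, which gives 95.4% (94.8% with the t distribution).
- 33% attrition leaves 32 × 0.67 ≈ 21 per arm. The t distribution gives 82.1% at d = 0.91 and 87.9% at d = 0.99.

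Both stated figures are reproduced to within about a point, so the sample size fits a single contrast.

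**2. Either visit suffices.** Familywise error = 1 − P(|Z₁| < 1.96 and |Z₂| < 1.96) for two correlated normal statistics: 9.1%, 8.4%, 7.8% and 7.0% at correlations 0.5, 0.7, 0.8 and 0.9. A null simulation gave 6.1% to 8.5%. It used 20,000 trials per setting, 32 per arm, visits at 0, 3 and 6 months and complete data. Assumed SDs were 18 kg at baseline, 0.4–0.7 kg/month for slopes and 0.5–2 kg residual. The correlation between the 3- and 6-month changes was 0.60 to 0.96.

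**3. Either interaction term suffices.** With complete data at 0, 3 and 6 months, the fitted linear slope is (y₆ − y₀)/6, so the 3-month value drops out. The quadratic contrast is y₀ − 2y₃ + y₆. The same simulation gave 9.6% to 9.7% if either could count. Two independent tests would give 1 − 0.95² = 9.75%.

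**4. Rules that control the error.** Requiring both visits gave 1.2% to 3.4%. One omnibus 2-df time-by-group test gave 4.9% to 5.0%.

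**5. Effect of a purely linear form.** Take the d values as between-arm effects (flat control arm, common SD).
- Points (0, 0), (3, −0.99), (6, −0.91): slope = 3 × (−0.91) / 18 = −0.152 per month. The fitted 3-month change is −0.455 against −0.99. The 6-month change is −0.91, as it should be.
- Adding (12, −0.74): mean time 5.25, mean value −0.66, Sxx = 78.75, Sxy = −17.31 + 13.86 = −3.45. The slope is −0.0438, so the fitted 6-month change is −0.26 against −0.91.

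**6. Price of keeping both visits.** Bonferroni at 2.5% each gives 90.7% power per contrast at d = 0.91 with 32 per arm and 73.0% with 21, below the stated 83% to 87%.

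**The case against.** The strongest reply is that this is a journal article, and that time form, time coding, final contrast and multiplicity rule are commonly left to a SAP, which is not shown. That would answer a complaint about silence. It does not fully answer this one: the article does state an analysis, and it states the time points in two ways. A SAP would have to choose between them.

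Other objections stand, and they limit the point. A reader might infer any of the following, and the document does not support them.

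- **That the overall group effect counts as efficacy.** The Hypothesis 2.1 label sits on the interaction alone; the group effect is only a listed model term. Accepting it as well would take the error to 14.1–14.4%, but nothing says it would be accepted.
- **That the curve's shape will be picked from the data.** No selection rule is stated. Linear and nonlinear terms could both sit in one model.
- **That the model does not test what was powered.** It names a group difference in change, which is the kind of parameter used for the sample size. Only the visit and the scale (percent or kg) are unstated.
- **That the falling d values prove weight regain.** They are medians of standardised effects, and different SDs or different studies at each time could produce the fall.

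The linear-fit figures likewise apply only if the nonlinear term is dropped. With three visits a quadratic mean is saturated and would reproduce the 3-month difference.

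**Conclusion.** The point holds in a limited form. The article fixes neither one visit nor one interaction contrast for weight, and its growth model extends beyond the randomised comparison.

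It would be tempting to conclude that type I error is inflated. The text supports only a conditional statement: about 6–9% if either visit suffices and 9.6–9.7% if either interaction term does, but at or below 5% if both visits are required or one omnibus test is used. The article commits to none of these rules, and its wording of the hypothesis can be read as requiring both visits.

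The error rates rest on an assumed two-sided 5% per test, and the simulated ones also on complete data and assumed variances. The linear-form figures rest on a flat control arm and a common SD. The point is worth acting on because the change is small and the power statement already presumes a single contrast.

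**What to change.** Name one primary contrast: the between-arm difference in weight change from baseline to 6 months, the end of the randomised period, tested at two-sided 5%.

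- **Model.** Use a mixed model of weight with visit (0, 3, 6 months) as a category, arm-by-visit terms, unstructured covariance and a common baseline mean. To report the effect as a percentage, model log weight and back-transform. Percent change itself cannot be the outcome here: it is zero for everyone at baseline, which makes the unstructured covariance singular.
- **3 months.** Make it secondary, tested only if 6 months is significant.
- **Overall group effect.** State that it is not an efficacy test.
- **Time points.** Reconcile Statistical Methods with Hypothesis 2.1 so that the between-arm comparison stops at 6 months. The 12-month data remain in use for Hypothesis 2.2.

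**Cost.** The changes are to wording only, with no change in sample size. Three visits already saturate a quadratic mean, so treating visit as a category adds no mean parameters over a quadratic model. The 95% power still applies at d = 0.91. At the 23% attrition quoted for 6 months, about 24 per arm remain (32 × 0.77 = 24.6), and power is 87.0% by the t distribution. The downside is that the 3-month result loses its primary status.
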